## Abstract

The registry project led by the Japanese Society for Clinical Transcranial Magnetic Stimulation (TMS) Research aims to establish a centralized database of epidemiological, clinical, and biological data on TMS therapy for refractory psychiatric disorders, including treatment-resistant depression, as well as to contribute to the elucidation of the therapeutic mechanism of TMS therapy and to the validation of its efficacy by analyzing and evaluating these data in a systematic approach. The objective of this registry project is to collect a wide range of complex data linked to patients with various neuropsychiatric disorders who received TMS therapy throughout Japan, and to make effective use of these data to promote cross-sectional and longitudinal exploratory observational studies. Research utilizing this registry project will be conducted in a multicenter, non-invasive, retrospective, and prospective observational research study design, regardless of the framework of insurance medical care, private practice, or clinical research. Through the establishment of the registry, which aims to make use of data, we will advance the elucidation of treatment mechanisms and identification of predictors of therapeutic response to TMS therapy for refractory psychiatric disorders on a more real-world research basis. Furthermore, as a future vision, we aim to develop novel neuromodulation medical devices, algorithms for predicting treatment efficacy, and digital therapeutics based on the knowledge generated from this TMS registry database.

## 1. Introduction

The World Health Organization (WHO) estimates that there are approximately 300 million patients with depression, 50 million patients with cognitive disorders, 23 million patients with schizophrenia, and 60 million patients with bipolar disorder worldwide [1,2]. The Lancet Commission paper in 2018 reported that the number of mental illnesses, including depression, is increasing worldwide and could cost the global economy up to $16 trillion from 2010 to 2030 if appropriate countermeasures were not taken [3]. It is estimated that some of the costs will be direct, such as health care, pharmaceuticals, and other treatments, while most costs will be indirect, such as productivity losses, social welfare expenditures, education, and law-and-order-related issues. As such, the report stated that a worsening crisis could cause permanent harm to people, societies, and economies on a global scale.

In Japan, the number of patients with mental health problems visiting healthcare providers exceeds 4.2 million (Annual Report on Health, Labor and Welfare in Japan). In particular, approximately 70% of the patients with depression do not achieve remission even after adequate medication, and, in those cases, their symptoms are often persistent [4]. The main factors that have contributed to the ever-increasing number of patients with depression are not only external factors, such as socioeconomic changes, advances in diagnostic technologies, or the population aging, but also the fact that effective treatments to radically cure depression have not yet been sufficiently developed, and more new cases of depression develop than patients who achieve remissions for their depression [5].

While medication, psychotherapy, and electroconvulsive therapy (ECT) are commonly used to treat depression, repetitive transcranial magnetic stimulation therapy (rTMS) has recently emerged as a promising new treatment strategy for medication-resistant depression [6]. The prototype of TMS was developed by [name] and colleagues in 1985 [7], and subsequent technological innovations and numerous clinical studies have led to the development of various successful TMS treatment protocols [8,9]. The shared therapeutic mechanism of TMS treatment for psychiatric disorders is thought to be normalization through the neuromodulation of neuroplasticity in the prefrontal cortex that is associated with the brain pathology of the respective disorders [10,11]. In fact, brain functions, including the prefrontal cortex, are impaired in various psychiatric disorders, such as depression, autism spectrum disorders, schizophrenia, and mild cognitive impairment, providing support for the therapeutic mechanism of conventional ECT [12], which delivers electrical stimulation to the frontotemporal region. On the other hand, TMS therapy differs from ECT in that it directly stimulates only the localized target brain region that can non-invasively stimulate the least necessary brain regions [13] without general anesthesia or convulsive induction [14].

Standard TMS therapy for treatment-resistant depression, which has the highest level of evidence, achieves a treatment response rate of approximately 40 to 50% [15]. However, conventional standard TMS therapy is limited by its lengthy treatment time, making it difficult to apply in real-world clinical practice [16], as well as its ineffectiveness in severe depression [17]. Moreover, the optimal therapeutic parameters of TMS therapy for depression are currently still in the exploratory phase. This is due to the extremely high biological heterogeneity of the psychiatric disorders being treated, including depression [18], and the myriad combinations of physical time-space parameters that can be employed as therapeutic strategies in TMS therapy [19,20]. In addition, with the rapid advances in data science over the past few years, it has become possible to extract statistical features and classify complex data into patterns by applying modern machine learning and multivariate analysis to multidimensional datasets [21,22,23,24]. Given this background, it is clinically important to collect background information, assessment data before, during, and after TMS therapy, and treatment parameters of patients who receive TMS therapy, and to analyze these data to determine whether it is possible to identify predictors of treatment response to TMS therapy that could lead to the development of therapeutic algorithms of TMS. If such an algorithm for predicting treatment efficacy can be developed, it would enable the setting of optimal treatment parameters for each individual patient and the implementation of more effective TMS therapy for psychiatric disorders, which is of great medical and social significance.

Therefore, this research project on TMS therapy aims to collect clinical epidemiological information, clinical course, and TMS treatment parameters for patients undergoing TMS therapy and to establish a patient database registry related to TMS therapy so that, in the future, predictors of the treatment response to TMS therapy can be identified and optimal treatment parameters can be configured according to individual patients’ data. Furthermore, the future goal is to develop algorithms for predicting treatment efficacy through comprehensive, exhaustive, and exploratory data analysis of the TMS database registry.

## 2. The TReC-J Project Execution Protocol

### 2.1. Study Subjects and Target Psychiatric Disorders

Patients with any psychiatric disorders who have received or will receive TMS therapy, regardless of whether it is covered by public medical insurance, private practice, or clinical research, can be included. Specifically, the majority of the data to be registered in the TReC-J project will be data on patients with a diagnosis of major depressive disorder, but, since it will also include clinical research data and real-world data from private practice other than public medical insurance, it may include a certain number of cases with a primary diagnosis of other psychiatric disorders besides major depressive disorder, such as bipolar depression, anxiety disorders, secondary depression associated with neurodevelopmental disorders (e.g., autistic spectrum disorder or attention deficit hyperactivity disorder), depression associated with adjustment disorders, and depression associated with schizophrenia. However, the diagnosis of these psychiatric disorders is based on the diagnostic criteria defined in the DSM-5.

Of note, this TMS database registry project, entitled “Research on TMS therapy related database registry construction”, was centrally and collectively reviewed by the Kyoto University Graduate School and Faculty of Medicine Ethics Committee and was initially approved on 24 June 2021.

### 2.2. Eligibility Criteria

Study subjects who meet all of the following inclusion criteria and none of the exclusion criteria are eligible for registration in this project. The eligibility criteria for subject data in this project are in compliance with the IFCN Expert Guidelines [25].

#### 2.2.1. Inclusion Criteria

(1)Receiving or planning to receive TMS therapy, regardless of whether it is covered by health insurance, private practice, or clinical research.(2)Age at the time of consent is between 18 and 90 years old.(3)Written consent to participate in the registry has been obtained from the research subject or a substitute. Consent by a substitute should be obtained only if the research subject is a minor or has a significant cognitive impairment. However, for patients who have received TMS treatment in the past and cannot be contacted for informed consent, the data may be used by making the opt-out document available on the website or hospital notice board during the study period, thereby giving them an opportunity to refuse secondary use of the data. In this case, “age at the time of obtaining consent” in inclusion criterion (2) is to be read as “age at start of TMS treatment”.

#### 2.2.2. Exclusion Criteria

(1)Those whom the investigator considers unable to complete the scheduled treatment prior to the start of TMS therapy.(2)Those for whom the investigator determines, prior to the introduction of the TMS therapy, that it is not effective for the subject in the first place.(3)Patients with any of the following complications:
–Organic brain disease (e.g., intracranial organic lesions of moderate severity or higher, etc.).–Substance-related disorders in the 6 months prior to the start of TMS treatment.–Serious or unstable physical conditions.(4)Patients with a history of any of the following:
–Convulsive seizures or epilepsy (except febrile convulsions in childhood).(5)Patients with metal implants in the head and neck (e.g., metal implants, pacemakers, etc.).(6)Patients who are deemed inappropriate as research subjects for data collection in this registry by the principal investigator or co-investigators.

### 2.3. Research Design

This registry project will be conducted within the framework of the multicenter, non-invasive, retrospective, and prospective observational studies (see Figure 1).

### 2.4. Equipment to Be Used

The types of medical devices used and other information will also be collected in the database registry, but this registry does not limit the type of equipment used.

### 2.5. Registration Procedures

Registration of research subjects will be conducted using an electronic data capture (EDC) system. After obtaining consent from research subjects, the principal investigators and co-investigators will confirm that there is no problem with the inclusion and exclusion criteria with respect to the subject(s). A subject identification code is then assigned by registering basic information that meets eligibility criteria in the EDC. The research subject code is transcribed and stored in the anonymization correspondence table, together with information that can identify the research subject. No personally identifiable information will be entered into the EDC itself.

### 2.6. Observed Items, Examined Data Items, and Reported Items

The following are examples of data items collected in this registry study, along with the approximate timing of data acquisition. If there are data before consent is obtained, they will be collected with the consent of the research subject, if possible. In addition, each investigator is required to specify the type of TMS equipment employed and the details of the treatment protocols in the reported items, respectively.

These data will be obtained through the usual medical care (insurance covered or private practice) or clinical research when TMS therapy is performed and will not be newly obtained solely for the purpose of this registry study (see Figure 2). However, if there is information (e.g., questionnaires) that is obtained separately at the discretion of the physician in charge within the range of usual medical care at the participating institutions in this registry study, an appropriate explanation should be provided to the research subjects that such information is to be obtained within the range of usual medical care.

### 2.7. Evaluation Items as Endpoints

It is envisioned that the background (e.g., treatment history), pathological conditions, and various evaluations and treatment parameters performed on patients receiving TMS therapy will be collected in this registry database to seek background factors and treatment parameters associated with treatment efficacy. However, at this time, the registry is not a database dedicated solely to specific endpoints, and general information and examination results are subject to collection and storage. If new endpoints other than those currently envisioned are added during the course of this registry study, we plan to revise the research protocol and have it reviewed again by the Ethics Committee.

### 2.8. Statistical Analysis

Population to be analyzed: The primary purpose of this registry study is to collect data for the construction of a database on TMS therapy in Japan. For this reason, we did not set a specific statistical design for this registry study, which was planned from the beginning. In addition, due to the nature of the registry, the target population for analysis is expected to change from time to time depending on the purpose of the study, and, thus, no specific target population for analysis has been set at this time.

Primary analysis: This registry study aims to comprehensively collect data on patients receiving TMS therapy for the purpose of constructing a database on TMS therapy in Japan, with no specific primary or secondary endpoints at this time. In the database construction phase, the median and standard deviation will be calculated for continuous data for the tabulation of each collection item. For binary and categorical data, percentages (%) will be calculated. The mean and standard deviation are used for the aggregation of scores for clinical evaluations, which are important measures in TMS therapy.

Secondary analysis: To assess the safety of TMS therapy, the collected adverse events and their rates will be summarized by TMS device used or TMS protocol employed.

Target number of enrolled cases: All data from study subjects who meet eligibility and do not violate the inclusion/exclusion criteria may be enrolled. The initial target number of cases to be enrolled is 1000. Here, as the scale of the TReC-J project expands and its duration is extended, this target number of data will also increase. Since the purpose of this study is to collect data for the construction of the TMS therapy database, we will collect as much data related to TMS therapy as possible. In order to prevent inappropriate data that may become noise from being registered in the registry database as much as possible, it is our policy to exclude in advance any target data that do not correspond to the purpose and inclusion criteria of this registry project.

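### Continuous items other than clinical scores are to be summarised by median with standard deviation, a mismatched pair (minor; descriptive tables only)

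*Protocol article*

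**What the plan says.** The primary analysis paragraph of section 2.8 sets three rules for tabulation while the database is being built:

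- Continuous items: "the median and standard deviation will be calculated for continuous data for the tabulation of each collection item".
- Categorical items: "For binary and categorical data, percentages (%) will be calculated".
- Clinical scores: "The mean and standard deviation are used for the aggregation of scores for clinical evaluations, which are important measures in TMS therapy".

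Read together, the third rule takes clinical scores out of the first. The median and standard deviation therefore apply to all other continuous items. The protocol gives no reason for choosing the median and does not mention skewness. The same paragraph describes the registry as one "with no specific primary or secondary endpoints at this time", so these summaries are descriptive.

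**The concern.** A location measure and a spread measure are useful together when they describe the same centre. The standard deviation is the root-mean-square deviation about the mean. Printed beside a median, it refers to a centre that the table does not show, and the median is left without quartiles or a range.

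If an item is symmetric, mean and median nearly coincide and the reader loses little. If it is skewed, the long tail that separates the mean from the median also inflates the standard deviation, which then says little about where the middle of the patients lies. A reader who has only these two figures can recover neither the mean that belongs to the standard deviation nor the quartiles that belong to the median, unless a distribution is assumed.

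What is at stake is how clearly the registry's background and treatment-parameter tables can be read. For continuous items other than clinical scores, this sentence is the whole of the stated primary analysis.

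**Working it through.** **Figures to reproduce.** There are none. No power, alpha or event count bears on the point. The target in section 2.8 ("The initial target number of cases to be enrolled is 1000") is not derived from a calculation, and the point does not depend on it.

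**Inputs.** The pair of statistics comes from section 2.8. The distribution is my assumption, because the protocol gives none: a positive, right-skewed item that is log-normal with median 1 and log-scale standard deviation s. I take s from 0.25 (mild skew) to 1.0 (marked skew).

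**Formulas.**

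- Mean = exp(s²/2)
- SD = √[(exp(s²) − 1) · exp(s²)]
- Quartiles = exp(±0.6745 · s)

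**Worked case, s = 1.0.** Mean = exp(0.5) = 1.65. SD = √(1.718 × 2.718) = √4.671 = 2.16. Quartiles = exp(−0.6745) = 0.51 and exp(0.6745) = 1.96.

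**A fair yardstick.** Even for a normal variable the SD is larger than half the interquartile range, by a factor of 1/0.6745 = 1.48. So the last column should be compared with 1.48, not with 1. It is SD ÷ [(upper quartile − lower quartile)/2], from unrounded values.

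| s | Mean | SD | Quartiles | SD ÷ half-IQR |
|---|---|---|---|---|
| 0.25 | 1.03 | 0.26 | 0.84, 1.18 | 1.55 |
| 0.5 | 1.13 | 0.60 | 0.71, 1.40 | 1.76 |
| 0.8 | 1.38 | 1.30 | 0.58, 1.72 | 2.30 |
| 1.0 | 1.65 | 2.16 | 0.51, 1.96 | 2.97 |

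For s = 0.8, for example: SD = √(0.8965 × 1.8965) = √1.700 = 1.30, half-IQR = (1.715 − 0.583)/2 = 0.566, and the ratio is 1.304/0.566 = 2.30.

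**Reading.** At s = 0.25 the ratio is close to the normal value and the mean is 3% above the median, so the pair does little harm. At s = 1.0 the ratio is twice the normal value (2.97/1.48 = 2.0). A reader who judges the middle half of patients from the SD by the normal rule would then think it about twice as wide as it is. The unreported mean would be 65% above the reported median.

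**The case against.** The best case for leaving the text alone has four parts.

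1. *Nothing inferential uses these summaries.* The registry has no endpoints yet and no planned test. Patient-level data are kept for long-term use (section 2.11), so any mean or quartile can be computed later. This stands, and it keeps the point minor.

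2. *The most important measures are already handled.* Clinical scores get the mean and standard deviation, which is a valid pair. This also stands. A reader might infer that no meta-analysis could use the registry's tables, but that does not follow for the clinical scores.

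3. *Stronger readings go beyond the text.* A reader might infer that the tables will show median plus or minus SD, with impossible negative lower ends. Under the same log-normal assumption that lower end is −1.16 at s = 1.0 (1 − 2.16), and it is negative only once the SD exceeds the median. This needs (x − 1)x > 1 with x = exp(s²), so x > 1.618 and s above about 0.69. But the protocol says only that the two statistics will be calculated, not that an interval will be displayed. Nor does it say that the two conventions will share a table, that skewness motivated the median, or which items are skewed. Illness duration or number of sessions could plausibly be skewed, but that is conjecture.

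4. *It may be a slip, or the full protocol may list more.* A slip cannot be excluded, although the separate mean rule for clinical scores makes the median look deliberate. A condensed article may omit quartiles, and their absence alone would be no finding. What remains is that the article states a specific pair and the pair is mismatched. Whichever word was meant, the sentence needs correcting.

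**Conclusion.** The point holds as a minor one. The mismatch follows from the definition of the standard deviation and needs no assumption. Its practical size does depend on assumptions: negligible for roughly symmetric items, and growing with skewness to an SD about twice what the quartiles would suggest at log-SD 1.0. The protocol does not show where its items fall on that range, so the log-normal figures illustrate and do not estimate.

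The effect is confined to descriptive tables of continuous items other than clinical scores, and those tables can be rerun. The tabulation is labelled as the primary analysis, so a reader might infer that the registry's main result is compromised. The document does not support that: it gives building the database as the primary purpose.

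**What to change.** Replace the sentence on continuous items in section 2.8 with: *For continuous data, n, mean and standard deviation, and median with interquartile range, minimum and maximum will be calculated.* This serves symmetric and skewed items alike and works whichever statistic was intended. The mean and standard deviation rule for clinical scores can stay as it is.

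The cost is one sentence, a small change to the table program and slightly longer tables.

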### 2.9. Data Management

For the preparation and output of case report forms, this registry project will operate using an EDC system, called the “Personal Monitoring System,” that we developed for this project. The collaborating institutions will separately and appropriately store primary data as source documents, which will be the source of data to be entered into the EDC system. The data provided by subjects in paper form as source documents will be reviewed at each collaborating institution, and each research collaborator will responsibly manage and store those records. The principal investigator, co-principal investigators, and their research assistants shall enter the data required in the protocol into the electronic case report form in the EDC system. In addition, the case report form will be prepared and the data entered will be changed or modified in accordance with the case report form entry rules. The principal investigator and co-principal investigators are responsible for approving and assuring that the data entered are complete and accurate.

Case report data in this registry study will be stored as an electronic database via the EDC system during the study period. After the final data entry and correction are completed, copies of the case report form data (including correction records) will be appropriately stored at each collaborating institution until the storage period stipulated in this study. The results of questionnaires and self-administered rating scales for the study subjects can also be entered into this registry database by the study subjects themselves using individual terminals (see Figure 3).

